#### Patient sample

Patients > 15 years of age with hospital-treated sepsis in 2016–2020 are included, as identified by the following strategies based on primary or secondary ICD-10-GM hospital discharge diagnoses (Table 1).

**Table 1 Tab1:** Sepsis definition criteria in health claims data

Year(s)	Sepsis and Infection ICD-10-GM Codes	Organ dysfunction ICD-10-GM or OPS Codes
2016–2019	R57.2 (septic shock) OR	
	R65.1 (severe sepsis) OR	
	At least one explicit sepsis code (A02.1, A20.0, A20.7, A21.7, A22.7, A24.1, A26.7, A28.2, A32.7, A39.1, A39.2, A39.3, A39.4, A40, A41, A42.7, A48.3, A49.9, A54.8, B00.7, B37.6, B37.7, B49, O75.3, O85, T80.2, T81.4, T88.0)	AND at least one ICD-10-GM code for organ dysfunction (J80.0, J95.1, J95.2, J96.0, J96.9, R09.2, D65, D69.57, D69.58, D69.59, D69.6, R57.8, E86, I95.9, I46.0, I46.9, R57.2, K72.0, K72.9, R17, N17.02, N17.03, N17.12, N17.13, N17.22, N17.23, N17.82, N17.83, N17.92, N17.93, F05, G94.32, K72.72!, K72.73!, K72.74!, R40, G93.4) OR OPS code for organ dysfunction (8–701,^a^ 8–704,^a^ 8–706,^a^ 5–311,^a^ 5–312,^a^ 8–800.6, 8–800.d, 8–800.f, 8–800.g, 8–800.h, 8–800.j, 8–800.k, 8–800.m, 8–800.n, 8–810.j, 8–810.x, 8 812.5, 8–812.6, 8–812.8, 8–771, 8–779, 8–852, 8–858, 8–821.2, 8–853.1, 8–853.3, 8–853.4, 8–853.5, 8–853.6, 8–853.7, 8–853.8, 8–853.x, 8–853.y, 8–854.2, 8–854.3, 8–854.4, 8–854.5, 8–854.6, 8–854.7, 8–854.8, 8–854.x, 8–854.y, 8–855.1, 8–855.3, 8–855.4, 8–855.5, 8–855.6, 8–855.7, 8–855.8, 8–855.x, 8–855.y, 8–856, 8-85a.0, 8-85a.1)
2020	R57.2 (septic shock) OR	
	At least one explicit sepsis code (see above)	AND R65.1 (SIRS with organ dysfunction) OR
	At least one explicit sepsis code (see above)	AND at least one ICD-10-GM code for organ dysfunction (see above) OR OPS code for organ dysfunction (see above) OR
	J09 OR J10 (laboratory confirmed Influenza) OR U07.1! (laboratory confirmed SARS-CoV2-infection)	AND at least one ICD-10-GM OR OPS code for organ dysfunction (see above)

*Abbreviations*: *ICD-10* International Classification of Diseases Version 10, German Modification, *OPS* German Procedure Classification, Operationen- und Prozedurenschlüssel

^a^codes were included in the definition if at least one hour of mechanical ventilation was documented in the course of the hospitalization

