#### Measurements

The module focuses on the three main points of the treatment pathway for sepsis patients: (A) pre-hospital care, (B) inpatient care, and (C) post-acute care.(A)Pre-hospital care: Pre-hospital health care utilization of patients with community-acquired sepsis in the 30 and 7 days prior to hospital admission is assessed. Specifically, contacts with the outpatient care system are analyzed, for example, how often the general practitioner, any outpatient specialist or the statutory health insurance emergency service were consulted, what laboratory or Point of Care Testing (POCT) diagnostics were performed, and if any initial anti-infective therapy was prescribed. For these outpatient contacts, the time latency between the last contact and the following inpatient admission with sepsis is assessed. Furthermore, we analyze which proportion of sepsis patients had pre-sepsis hospitalizations or emergency department visits, as well as which proportion of sepsis patients was admitted as emergency to their index treatment, and for which admission diagnosis.(B)Inpatient care: For the index hospitalization, we assess treatment characteristics, e.g. which organ replacement therapies were conducted, if patients received any immune absorbent therapy, if an intensive care complex or palliative care treatment was administered; as well as the departments involved in sepsis care. We identify inter-hospital transfers and characterize hospitals involved in the chain of sepsis care by the following key characteristics: type of hospital ownership (owned by local or federal state authorities, private for-profit organizations, or by voluntary charitable organizations or churches) number of hospital cases and beds, region (urban/rural), number of cases with (complex) intensive care complex treatment.(C)Post-acute care: Post-acute care utilization is assessed starting at the day of discharge from the last interhospital-transfer from the index hospitalization. We analyze long-term mortality, rehospitalizations (in general, for infectious diseases or recurring sepsis, for vaccine-preventable diseases, for ambulatory-care sensitive diagnosis), emergency department visits in hospitals or treatment by emergency services of the statutory health insurance emergency service, inpatient rehabilitation therapies, utilization of medical remedies, as well as outpatient consultations. We put special emphasis on the out-of-hospital intensive care and the conduction of long-term mechanical ventilation in that setting. Furthermore, psychotherapy and psychiatric medications are recorded and parameters concerning the return to work. Based on a detailed description of this post-acute sepsis care, we attempt to identify classes of health care utilization among sepsis survivors, examine whether such classes are constant or variable over time, and whether specific patient, sepsis, and treatment characteristics are associated with class membership.

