#### Measurements

(A) The PCR are first examined with regard to their documentation quality. This includes, for example, the frequency of missing values, invalid values or non-plausible values. Checks of vital signs are especially important in this process, since they are often not documented even in case of suspected infection or sepsis [25].

We will investigate the proportion of patients with a documented suspicion of sepsis in the pre-hospital setting and the symptoms of these patients. We analyze what proportion of patients with suspected sepsis already receive care by emergency physicians in the pre-hospital setting, and how the pre-hospital care of sepsis patients with and without the involvement of emergency physicians differs. In addition, we investigate which therapies are initiated in the pre-hospital setting if sepsis is suspected (e.g., drug administration, oxygen administration, ventilation, administration of antibiotics, fluid therapy, catecholamines, vasopressors).

(B) Based on the linked data, we assess in which sectors (e.g. outpatient treatment, inpatient admission to a hospital) of the health care system patients received follow-up care after EMS treatment, and if this care differs with respect to sepsis suspicion during EMS treatment. Further analysis will determine whether sepsis suspicion in the pre-hospital setting affects short- and long-term patient outcomes (e.g., ventilation, mortality, readmission due to specific diagnoses, need for new care).

In addition, sepsis-specific screening tools such as qSOFA and others [26, 27] will be operationalized based on available vital signs in PCR. The aim is to evaluate how precise the pre-clinical screening tools detect sepsis and if this precision changed over time compared to a clinically confirmed and coded sepsis diagnosis (defined in accordance to Module 1) during a subsequent hospitalization.

A special focus lies on false-negative classifications, i.e. patients without a pre-clinical suspicion of sepsis but confirmed sepsis diagnosis in health claims data. For this group, potential sepsis characteristics (e.g. organ dysfunction by qSOFA) or patient characteristics will be investigated in more detail.

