#### Statistical analyses

Data quality in the PCR is primarily examined with an exploratory approach. We plan to use methods for the assessment of data quality (e.g. visualization through heat maps). For analyses in (A) and (B) we use frequency counts, cross-tabulations, measures of location and dispersion measures.

The characteristics of pre-clinical sepsis screening tools are analyzed by using binary classifiers. Measures such as sensitivity, specificity, negative/positive predictive value, are calculated.

Additionally, descriptive measures and appropriate visualization techniques, such as Sankey plots, are utilized to depict pre-hospital patient pathways, including emergency care, inpatient admission or utilization of other health care sectors. This is performed for the total patient sample, but also for subgroups (e.g., by age, gender, comorbidity). In order to evaluate acute and long-term patient outcomes, module 2 employs descriptive and multivariate analysis methods, which are suitable for the data structure. Survival times of patients are investigated by using the Kaplan–Meier estimator.

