Our study has also limitations to consider. On the one hand, these arise from inherent limitations of research using health claims data, such as potentially incomplete, inaccurate, or missing data, and inability to adequately evaluate the appropriateness of care [37, 38]. Although health care utilization and costs can be researched with high validity, recorded incidences of diseases have to be considered as administrative as only diseases diagnosed and coded correctly during hospitalizations and outpatients visits can be detected. For sepsis, we know from previous validation studies that the coding of diagnoses captures cases only with low sensitivity, and misses cases with lower disease severity [39]. This fact may be aggravated by the change in sepsis-related ICD-10-GM codes in 2020 in Germany. We address this issue by applying different case identification strategies for the years 2016–19 and 2020 (Table 1), but still it is likely that our sepsis definition does not capture all sepsis patients treated in German hospitals.

In module 2, exclusively PCR of EMS from study regions in Bayern and Baden-Württemberg as well as from selected EMS organizations will be processed. Hence, all generalizations of study results with regard to these two federal states or to the entire health care system in Germany must be examined carefully.

Furthermore, undesired selection effects may be introduced into the database in case key variables needed for the linkage of PCR and health claims data are unavailable selectively (e.g. KVNR). However, it is known from previous studies [22] that data linkage with health claims data is possible even if the key variable KVNR is not available for some of the PCR.

Qualitative data curation in module 3 might be limited by the fact that since participants of the oral interviews are not sharing statements anonymously in interviews and SOFGs, statements might not be free from social desirability effects. The sample might be subject to self-selection bias as participation will be voluntarily. Moreover, interviews using a video conference system may not reach the same depth as face-to-face interviews as rapport building can be limited. However, using online video-supported interviews allow for a composition of groups without logistic concerns and geographical restrictions, which increases the groups ‘ diversity and quality.

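### Module 2 (B) puts no onset condition on the coded sepsis used as reference standard, so sepsis that began after EMS contact counts as missed

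*Protocol article*

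**What the plan says.** In Module 2, Measurements (B), screening tools built from vital signs in the patient care reports are compared with a "clinically confirmed and coded sepsis diagnosis (defined in accordance to Module 1) during a subsequent hospitalization". The same section singles out false negatives for closer study, defined as "patients without a pre-clinical suspicion of sepsis but confirmed sepsis diagnosis in health claims data". Module 2, Statistical analyses, adds: "Measures such as sensitivity, specificity, negative/positive predictive value, are calculated".

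The definition carried over is in Module 1, Patient sample, where cases are found "based on primary or secondary ICD-10-GM hospital discharge diagnoses", combined in Table 1 with organ-dysfunction codes. It contains no condition on when sepsis began.

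Module 1, Measurements (A), does make the distinction: "Pre-hospital health care utilization of patients with community-acquired sepsis in the 30 and 7 days prior to hospital admission is assessed". Module 2 does not repeat it.

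The limitations in the Discussion state that "the coding of diagnoses captures cases only with low sensitivity" and that less severe cases are the ones missed. They do not mention sepsis that starts after EMS contact.

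**The concern.** A screening tool or a crew can detect only what is present at the time of contact. Secondary discharge diagnoses describe the whole stay, so they also record sepsis that develops in hospital, for example after trauma or surgery. Module 2 data are not pre-selected for sepsis, so the linked file will include patients transported for other reasons. Any of them who later becomes septic in hospital is reference-positive and, if not suspected at contact, enters the false-negative group.

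That group carries weight. The Discussion presents the linked data as a way to explore how much sepsis goes unrecognized in EMS care and what this does to treatment and outcomes, and care recommendations are to be derived from the project. If part of the group had no sepsis at contact, three results are affected: the sensitivity estimate, the number of missed cases, and the profile of missed cases. The profile would show apparently sign-free sepsis that was not yet sepsis. A large sample does not reduce this bias.

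**Working it through.** **1. The plan's own figure.** Module 2, Sample size considerations, gives 2.8 million patient care reports, an AOK share of about 40% and a sepsis rate of 2–4%.
- 2.8 million × 0.40 = 1.12 million linked cases.
- 1.12 million × 0.02 = 22,400, and × 0.04 = 44,800.
- The article states 22,700–45,400, about 1.3% higher, which is rounding. This figure is not in dispute.

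**2. Apparent sensitivity.** Let h be the share of reference-positive cases whose sepsis began after EMS contact. Let Se and Sp be the sensitivity and specificity for sepsis present at contact. Patients without sepsis at contact are flagged at rate 1 − Sp, so:

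apparent Se = (1 − h) × Se + h × (1 − Sp)

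share of false negatives with no sepsis at contact = h × Sp / (1 − apparent Se)

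The article gives no value for h, Se or Sp. With assumed Se = 0.60 and Sp = 0.90:

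| h | Apparent Se | Share of false negatives with no sepsis at contact |
|---|---|---|
| 0% | 0.60 | 0% |
| 10% | 0.54 + 0.01 = 0.55 | 0.09 / 0.45 = 20% |
| 20% | 0.48 + 0.02 = 0.50 | 0.18 / 0.50 = 36% |
| 30% | 0.42 + 0.03 = 0.45 | 0.27 / 0.55 = 49% |
| 40% | 0.36 + 0.04 = 0.40 | 0.36 / 0.60 = 60% |

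In general, each 10 points of h lower apparent sensitivity by 0.10 × (Se − (1 − Sp)). Over Se 0.40–0.80 and Sp 0.85–0.95 this is 2.5 to 7.5 points. The effect is downward whenever Se exceeds 1 − Sp.

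If the 22,700–45,400 expected cases are read as reference-positive cases, h = 20% adds 22,700 × 0.20 × 0.90 = 4,086 to 45,400 × 0.20 × 0.90 = 8,172 false negatives with no sepsis at contact.

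**3. The opposing effect.** The Discussion says that coding misses milder cases. If these are also less often tool-positive, they drop out of the reference standard and sensitivity rises. Assume true Se 0.60, with 70% of tool-positive and 30% of tool-negative true cases coded:
- Observed Se = 0.60 × 0.70 / (0.60 × 0.70 + 0.40 × 0.30) = 0.42 / 0.54 = 0.78.
- Adding h = 20% at Sp 0.90: 0.80 × 0.778 + 0.20 × 0.10 = 0.64, still above 0.60.

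**4. Uncoded sepsis and specificity.** Assume 3% prevalence, Se 0.60, Sp 0.90, and a uniform coding sensitivity s. Observed specificity is 1 − (0.97 × 0.10 + 0.03 × 0.60 × (1 − s)) / (0.97 + 0.03 × (1 − s)). This gives 0.895 at s = 70% and 0.889 at s = 30%, so the effect is negligible.

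**The case against.** The strongest reply is that this is operational detail. The Project timeline says that analysis plans for modules 1 and 2 were prepared. These are not shown and may fix the onset rule and the interval. The article nowhere says that hospital-acquired sepsis is included; that follows from a definition without restriction. This has force for the interval. It has less force for onset, because the reference standard is stated affirmatively by pointing to the Module 1 case definition, and the one place where the study limits itself to community-acquired sepsis is a different analysis.

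A reader might infer that sepsis in any later stay counts, since the claims data reach at least a year past each EMS case. The wording does not support that. A stay following the EMS run most naturally means the one the run led to. The point survives on that reading, because secondary diagnoses still admit sepsis that began during that stay.

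A reader might also infer that reported sensitivity will come out too low. The documents do not support this either: the severity-dependent under-coding that the authors describe may push it upward, as step 3 of the working shows.

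Two further points stand. Low coding sensitivity is already disclosed as a limitation. And the false-negative definition quoted concerns documented suspicion, while the plan examines qSOFA signs within that group. This would help to separate patients with detectable signs from those without, but it does not show whether sepsis was present at contact.

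**Conclusion.** The concern holds as a defect in the stated definition. As written, the reference standard has no onset condition and the false-negative definition names no stay or window, so sepsis that began after EMS contact is counted as missed. This inflates the false-negative group and mixes in patients who had no sepsis to detect.

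Taken alone, it moves apparent sensitivity from 0.60 to between 0.55 and 0.40 for h of 10% to 40%, and 20% to 60% of the false negatives would have had no sepsis at contact. These figures rest on assumed Se 0.60 and Sp 0.90 and on an h that the article does not document. They show scale and are not estimates for this study.

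The net bias in sensitivity cannot be signed from the documents. A claim of material harm to specificity is not supported, since its shift is about 0.01 at most under the assumptions in step 4.

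**What to change.** For the accuracy measures and the false-negative analysis, make the primary reference standard sepsis classed as community-acquired, using the Module 1 (A) classification, in the hospital stay directly following the EMS contact. Apply the same rule to both analyses, and state how a stay is tied to an EMS contact. Report the unrestricted all-sepsis rule as a sensitivity analysis, so that readers see how much the results depend on it.

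The cost is analysis-plan wording and reuse of a distinction that the study already makes; no new data source is needed. There will be fewer reference-positive cases. The claims-based flag will misclassify some patients and, depending on how community-acquired is defined, may exclude sepsis after a recent discharge that was present at contact. The article does not show the operational rule, so it should be cited or stated where Module 2 uses it.

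Accuracy measures corrected over a range of coding sensitivity would be a useful addition but are optional.

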#### Statistical analyses

Data quality in the PCR is primarily examined with an exploratory approach. We plan to use methods for the assessment of data quality (e.g. visualization through heat maps). For analyses in (A) and (B) we use frequency counts, cross-tabulations, measures of location and dispersion measures.

The characteristics of pre-clinical sepsis screening tools are analyzed by using binary classifiers. Measures such as sensitivity, specificity, negative/positive predictive value, are calculated.

Additionally, descriptive measures and appropriate visualization techniques, such as Sankey plots, are utilized to depict pre-hospital patient pathways, including emergency care, inpatient admission or utilization of other health care sectors. This is performed for the total patient sample, but also for subgroups (e.g., by age, gender, comorbidity). In order to evaluate acute and long-term patient outcomes, module 2 employs descriptive and multivariate analysis methods, which are suitable for the data structure. Survival times of patients are investigated by using the Kaplan–Meier estimator.

### Module 3: Qualitative exploration of the patient and provider perspective on sepsis care

#### Design and data source

Module 3 consists of a qualitative approach focusing on (A) patients’ and their relatives’ as well as on (B) health care providers’ perspective on sepsis care. In 3 (A), semi-structured telephone interviews with patients and/or their relatives are planned to assess their individual perspective on pre-clinical, clinical, and post-acute care as well as their satisfaction with information and informational needs along this pathway. In 3 (B), health care professionals’ perspective is investigated using interdisciplinary focus group discussions, with a main focus on transsectoral transitions between pre-clinical, clinical, and post-acute care. For each transition (pre-clinical – clinical; clinical – post-acute care), 4 to 5 focus groups are planned. To inform the development of focus group guidelines, 9 upstream video-supported interviews with individuals of different health care professions involved in pre-clinical, clinical, and post-acute sepsis care are conducted.

#### Sample

Three (A) interview participants are recruited using advertising posts on social media platforms and flyer placement in the post intensive care unit of the Charité University Medicine Berlin. Patients >  = 18 years, who are fluent in German and who developed sepsis before a maximum of five years are eligible for participation. Patients are recruited until data saturation is being reached in the interviews. (B) Upstream interviews are planned with 9 health care professionals from different disciplines (pre-clinical: 3, clinical: 3, post-acute: 3). For the focus group discussion rounds, we aim to involve 6–8 participants per group, adding up to a maximum amount of 80 health care professionals in total. Each focus group will be multidisciplinary and cross-sectoral in the selection of participants. Participants for interviews and focus groups are identified by in-house databases as well as the website information of eligible institutions, and are contacted directly by phone or e-mail with an information flyer and additional details. Participation requires a professional experience of at least one year in the respective field. The participants receive an expense allowance of 60 Euro for the expert interviews and 120 Euro for the focus group discussions.

#### Measurement

(A) In line with our explorative, qualitative approach we intend to use open-ended questions. Thematically, the interview guides will be grounded on a systematic review carried out in advance as well as internal experts rounds and comprise topics like: Challenges, best practice examples, and deficits existing in acute and long-term care after sepsis, especially in the transitions between sectors. For details on the systematic review, we refer to the PROSPERO registration (CRD42023405681). (B) In upstream interviews, practices and subjective perceptions of sepsis care regarding four main thematic blocks (recognition, acute treatment, rehabilitation/aftercare, and transition of care, selected depending on the field of work of the interview participant) will be investigated using open-ended questions. An emphasis will be placed on perceived barriers and contributory factors to prompt and adequate care. Especially, desires for optimal care will be elaborated on. The interview guide development bases on a semi-systematic review of current literature. The drafted guide is discussed and revised within the project team as well as with a team of researchers and clinicians of different specializations at the Jena University Hospital, and pretested in a pilot interview. All upstream interviews will be audio-recorded, transcribed, and proofread.

Focus group discussions are centered on intersectoral transitions of care, particularly on multidisciplinary communication and collaboration among involved health care professionals, and aim to identify facilitators and barriers of successful intersector-transitions. In the course of the pandemic, new remote research approaches had to be established in which people interact without face-to-face contact [28]. This includes the development of asynchronous online focus groups (AOFG), which is a dynamic digital bulletin board method that takes place over a set number of days, e.g. 3 – 30 days [29] and where study moderators post different discussion prompts, and participants are able to respond at any time until the focus group closes [30]. In order to compare and evaluate synchronous and asynchronous online focus groups (SOFGs and AOFGs, respectively), we decided to use both approaches: AOFG for the transition pre-clinical to clinical care, and SOFG for the transition clinical to post-acute care [30]. Consequently, two separate but similar focus group guides are developed based on the upstream interviews and literature review. Each focus group guide will be pretested once. Due to the text format of AOFGs, transcription is not required. We use the Moodle platform of the Jena University Hospital for the AOFGs, from which data can be directly imported to MAXQDA. SOFGs are video-recorded, transcribed, and proofread. Both the interviews and focus groups are conducted by researchers experienced in qualitative research methods.

